## Measurement instruments

### Outcome variables

#### Self-reported work resumption

To measure work resumption, we make a distinction between being fit for work, work resumption, and sustainable work resumption. Being fit for work will be operationalized by not receiving disability benefits. Work resumption will be operationalized by being at work without receiving disability benefits (on a dichotomous scale), and by time to relapse. Time to relapse is defined as the duration of being at work until a participant is on sick leave again. Sustainable work resumption will be operationalized by being at work for at least three consecutive months without receiving disability benefits (on a dichotomous scale). In addition, the duration of work resumption will be measured (on a continuous scale). All these variables will be assessed using custom-made self-report questions. The custom-made questionnaires are presented in Additional file 1. In order to calculate the time to relapse and sustainable work resumption, we will ask the participants to indicate when they were incapacitated from work and when they resumed work. In addition, we will directly ask if the participant resumed work for at least three consecutive months.

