## Statistical analysis plan

Following an intent-to-treat approach, data from all included participants will be analyzed. Descriptive statistics will be used to explore the mean and median scores, and standard deviations of all measures. Depending on the type of dependent variable, we will apply Cox proportional-hazards regression analysis with time-dependent covariates or multiple (logistic) regression analysis, starting with a univariate analysis, followed by a multivariate analysis. If statistical power allows, interaction effect between time and all the predictor variables will also be tested to evaluate if the effect of the predictor variables is consistent in time. Additionally, we will check for site effects with the mixed model regression approach. All variables will be examined for the assumptions required for parametric analyses. Results will be evaluated at *p* < 0.05 significance level. Effect sizes (i.e., odds ratios) and post hoc power will be calculated when appropriate.

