### Primary objectives

Logistic regressions will be performed to examine the effect of preoperative as well as postoperative fear of movement-related pain and avoidance behavior (and their generalization), expectancies towards recovery, expectancies towards work resumption, presence of yellow flags, on return to work at 6 weeks, 3 months, 6 months, and 12 months post-surgery. Next, a time-dependent Cox regression will be performed to examine the effect of the predictor variables on return to work over time. The same analyses will be conducted for the sustainability of work resumption at 3 months, 6 months, and 12 months post-surgery as a dependent variable.

Multiple linear regression analyses will be carried out to examine the effect of the predictor variables on the duration to resume work over time. Log-rank test and Kaplan–Meier plots will be applied to compare rates of work resumption between participants with different profiles (i.e. at work or not during the different measurement moments).

All interaction effects, including the predictor*time interactions, will be explored. Following potential confounders will be included as covariates in each analysis: age, sex, work characteristics, duration of incapacity for work, surgery complication, and the potential influence of the COVID-19 pandemic.

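### Linear regression of time until work has no value for participants not back by 12 months, and it does not match the continuous work outcome the article lists

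*Protocol article*

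**What the plan says.** The section Self-reported work resumption lists several outcomes:

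- A dichotomous one: "Sustainable work resumption will be operationalized by being at work for at least three consecutive months without receiving disability benefits (on a dichotomous scale".
- Time to relapse: "Time to relapse is defined as the duration of being at work until a participant is on sick leave again".
- A continuous one, given no further definition: "the duration of work resumption will be measured (on a continuous scale".

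The section Primary objectives then names these analyses:

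- Logistic regression of return to work at each follow-up, after which "a time-dependent Cox regression will be performed to examine the effect of the predictor variables on return to work over time".
- For sustainability: "The same analyses will be conducted for the sustainability of work resumption at 3 months, 6 months, and 12 months post-surgery".
- Multiple linear regression to "examine the effect of the predictor variables on the duration to resume work over time".

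The opening of the Statistical analysis plan section states that "data from all included participants will be analyzed". Follow-up ends 12 months after surgery (Design).

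**The concern.** The linear regression has two problems.

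First, its outcome is how long a participant waits before working. The outcome section does not list that. The continuous measure it does list appears to be how long a participant stays at work, and no analysis is named for it or for time to relapse. A reader of the eventual results could not tell which quantity a reported duration effect refers to.

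Second, time until work is right-censored. All participants are on sick leave on the day of surgery (inclusion criteria), so everyone starts the clock. For anyone not back at 12 months, only a lower bound is known. Ordinary linear regression must either omit these people or treat 12 months as if it were an observed return. Omitting them means the effect of fear and avoidance is estimated only in those who succeeded in returning, and the failures to return are the very group the study wants to predict.

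**Working it through.** **1. Outcomes and analyses side by side**

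| Outcome listed | Named analysis |
|---|---|
| Work resumption, yes/no | Logistic, Cox |
| Sustainable resumption, yes/no | Logistic, Cox at 3, 6 and 12 months |
| Duration of work resumption, continuous | None under that name |
| Time to relapse | None named |
| (not listed) time until work | Multiple linear regression |

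**2. How many lack an observed value.** The Background cites 20% unable to resume work at 1 year in an earlier Belgian discectomy study, and return rates of 50–90% across studies. These are external rates, not assumptions of this plan. With 300 participants before dropout:

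- 20%: 300 × 0.20 = 60
- 10% to 50%: 300 × 0.10 = 30, to 300 × 0.50 = 150

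**3. The plan's own sample size, then the reduced one.** The power calculation is for multiple linear regression, with f² = 0.13 / 0.87 = 0.1494, numerator df 14, alpha 0.05 and power 90%. Power is the probability that a noncentral F with df (14, N − k − 1) and noncentrality f² × N exceeds its 5% critical value. With k = 14, N = 167 gives 0.902, so the stated 167 reproduces. Keeping f² fixed and using only those who resumed:

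| Available | Share not back | Usable | Power |
|---|---|---|---|
| 300 | 20% | 240 | 0.99 |
| 167 | 20% | 133 | 0.79 |
| 150 (300 after 50% dropout) | 20% | 120 | 0.73 |
| 167 | 10% | 150 | 0.86 |
| 167 | 50% | 83 | 0.50 |

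The row with 150 assumes that dropout and non-resumption are unrelated.

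**4. Direction of the bias (illustration, inputs assumed).** Return times are exponential, with 80% back by 12 months at the average predictor value, so the hazard is −ln(0.2) / 12 = 0.134 per month. The hazard ratio is 0.7 per SD of a predictor. About 21% are then not back at 12 months. The slope of log time on the predictor is 0.35 when every return time is known (theory: −ln 0.7 = 0.357). Among those back by 12 months it is 0.16. People with high predictor values stay in the analysis only if they happened to return early, which flattens the slope. Together with the smaller sample in step 3, this means the fixed-f² power figures there are optimistic for this outcome.

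**5. Are the two durations interchangeable?** Without relapse, time at work within the window equals 12 minus time until work, so the correlation among resumers is −1. In the same simulation, assumed relapse hazards of 0.02 to 0.10 per month give correlations of −0.83 to −0.50. The measures run in opposite directions, and once people relapse one cannot stand in for the other.

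**The case against.** **The term may be loose.** The listed duration of work resumption is undefined and could simply mean time to resumption. That would remove the mismatch between the two sections. It would not remove the censoring problem, and time to relapse would still have no named analysis.

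**This is a condensed article.** Rules for non-resumers and the derivation of outcomes may sit in a full analysis plan that is not shown, and the work questions are in an additional file. The general analysis text also says the model depends on the type of outcome and lists Cox regression, which would suit time to relapse. This has force for time to relapse, which is the weakest part of the point. It has less force for the regression: the article itself states linear regression for a censored time, so this is a choice made rather than a detail left out.

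**The main analyses already cope.** The planned Cox regression and Kaplan–Meier plots can treat non-resumers as censored. This stands and confines the problem to the linear regression.

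**Readings that go too far.**

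- A reader might infer that sustained work is never analysed. The defined sustainable-resumption measure is dichotomous, and it is analysed by logistic and Cox regression.
- A reader might think time at work is the measure that lacks a value for non-resumers. It is naturally 0 for them; the unobserved quantity is time until work.
- A reader might take the cited 20% as people who never resume. It is an external rate at 1 year.
- A reader might treat the opposite signs as an error in themselves. They are only reversed scaling, provided the outcome is labelled clearly.
- A reader might conclude that time until work misses more than half of the variance in time at work. Figures of 56–76% arise from an assumed mean return of 2.2 months, which leaves only exp(−12 / 2.2) = 0.4% not back at 12 months and cannot be combined with a 20% rate. The same exponential model set to 20% gives about 22–40% for yearly relapse of 15–30%. The documents give no return-time or relapse distribution to settle this.

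**Conclusion.** The point holds for one analysis. The linear regression of time until work does not use the continuous outcome as listed, and it has no observed value for those not back by 12 months. Their share is 10–50% on the cited external rates. Limiting the model to resumers contradicts the intention to analyse all included participants and tends to shrink predictor effects. The size of that shrinkage (0.35 to 0.16 in the illustration) rests on an assumed exponential return curve and hazard ratio; its direction follows from selecting on early return. At 20% not back, the 167 needed for 90% power would yield 133 usable participants and power of about 0.79, even with the effect size held fixed.

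The mismatch itself depends on reading the undefined duration as time at work, which is the natural but not the only reading. The logistic and Cox analyses of return to work and of sustainable resumption, which carry the primary objective, are not touched. The change is worth making because it is cheap and the regression as written is the wrong tool for this outcome.

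**What to change.** - **Primary objectives:** remove the linear regression of time until work. Analyse that outcome only with the Cox model already planned, censoring participants not back at their last follow-up.
- **Self-reported work resumption:** define the duration of work resumption. If it means time at work, make it the linear-regression outcome, as days at work without disability benefits from surgery to 12 months, with 0 for followed participants who have not resumed. Use robust or bootstrap standard errors.
- **Time to relapse:** name a secondary analysis among resumers, with censoring of those still at work at last follow-up, and say that it is conditional on having returned.

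The cost is wording in two sections and one variable derived from the incapacity and resumption dates that participants are already asked for. There are two downsides. Days at work is skewed with a spike at 0. Participants lost before 12 months have no complete total and must go through the plan's missing-data handling rather than be scored 0; with dropout put at up to 50%, that group may be large.

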## Methods

### Design

This multisite study has a prospective, longitudinal design in which individuals with radicular pain who undergo a lumbar decompression, will be followed prior to surgery up until 1 year post-surgery. Measurements take place prior to surgery (preoperative measurement), immediately after surgery (postoperative measurement), and 6 weeks, 3 months, 6 months, and 12 months post-surgery (follow-up measurements), see Fig. 1. The expected duration of the entire study is approximately 2 years.

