### Participants

Three hundred individuals with radicular pain will be recruited. Every participant will be planned for back surgery in one of the nine involved Belgian hospitals (i.e., University Hospitals Leuven, Ziekenhuis Oost-Limburg, Noorderhart Mariaziekenhuis, AZ Groeninge, GasthuisZusters Antwerp, Centre Hospitalier de Wallonie picarde, Imeldaziekenhuis, Regional Hospital Heilig Hart Tienen, and AZ Sint-Lucas Ghent). Inclusion criteria are: (a) age between 18 and 55, (b) proper mastery of the Dutch, English, and/or French language, (c) intermittent or constant invalidating lumbosciatica for less than 1 year prior to the planned surgery, operationalized by being on sick leave on the day of the surgery (documented by the surgeon), (d) radicular pain in the leg(s) due to compression, that will be treated surgically by performing a decompression without it leading to fusion and/or fixation, and (e) self-employed or has an employment contract, and is on sick leave for less than 1 year at the day of the surgery. Reasons for exclusion are (based on self-report): (a) being treated (ambulant or residential) for substance abuse, suicidal ideation, or a psychotic disorder in the year before the consult with the surgeon, (b) at least one back surgery in the last 5 years prior to the planned surgery, and (c) presence of a comorbid condition (e.g. a severe neurological deficit, a pulmonary embolism, permanent paralysis, and another pain problem in the limbs), which may affect the pain, the outcome of the surgery, the duration of the rehabilitation, and/or the participant’s capacity to return to work during the course of the study. At the end of the study, participants will receive a gift voucher worth of maximum 40 euros (at a rate of 10 euros per completed follow-up measurement).

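### The log-rank and Kaplan-Meier groups are defined by work status at follow-up, which is the outcome itself, so the test is significant largely by construction and says nothing about the predictors

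*Protocol article*

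**What the plan says.** The relevant statements in the protocol article are these.

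- **Primary objectives** (statistical analysis plan). Log-rank and Kaplan-Meier methods are planned to "compare rates of work resumption between participants with different profiles (i.e. at work or not during the different measurement moments"). The bracket defines the profiles. No predictor-based profile is named for this test.
- **Self-reported work resumption.** "Work resumption will be operationalized by being at work without receiving disability benefits (on a dichotomous scale"), and also by time to relapse. Relapse is allowed for: "Time to relapse is defined as the duration of being at work until a participant is on sick leave again".
- **Participants.** An eligible person is employed or self-employed and "is on sick leave for less than 1 year at the day of the surgery". Sick leave on the day of surgery is also how another inclusion criterion is operationalized.
- **Design.** The measurement moments at which work status is recorded are "6 weeks, 3 months, 6 months, and 12 months post-surgery (follow-up measurements"), all after surgery.
- **Statistical analysis plan**, opening paragraph. "Results will be evaluated at *p* < 0.05 significance level".

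**The concern.** A log-rank test asks whether groups fixed at the start of follow-up have the same event rate over time. Here the groups are not fixed at the start. A person counted as at work at 3 months has already had the event. A person counted as not at work has either not had it or has had it and relapsed. Apart from relapse, nobody in the second group can have an event before the grouping visit, which is immortal time.

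The null hypothesis is therefore false by definition, whatever the predictors do. A very small p-value would be reported under the primary objectives, judged at the 5% level, and a reader could take it as evidence on psychological profiles. It would show only that people who were back at work had gone back to work.

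**Working it through.** **Figure in the plan.** The article states none for this test. Its one computed size, 167, is for multiple linear regression. It reproduces with 14 numerator degrees of freedom (power 0.902) and has no bearing here.

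**Inputs.**

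- 82% back at work at 3 months: cited in the Back surgery section.
- 300 enrolled, 50% dropout: Sample size section. 300 × 0.5 = 150 completers.
- Visits at weeks 6, 13, 26 and 52: Design section.
- Share never returning: 10%, assumed. The article cites 20% not back at 1 year, but from a different study; that figure and 82% back at 3 months cannot both hold in one cohort without relapse.
- Relapse: no rate given, so 0 to 50% is assumed, with 70% and 90% as extremes. Relapse is independent of everything else.

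**By hand, 3-month grouping, no relapse, n = 150.**

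1. At work: 0.82 × 150 = 123. Not at work: 27.
2. Up to month 3 all 123 events fall in the at-work group and none in the other. The number at risk falls from 150 to 28, with the 27 always among them.
3. Expected events in the off-work group: Σ 27/k for k = 28 to 150 = 45.9. Observed: 0.
4. Variance: Σ (27/k)(1 − 27/k) over the same k = 24.2.
5. After month 3 only the off-work group is still at risk, so nothing is added to the difference or the variance.
6. Chi-square = 45.9² / 24.2 ≈ 87 on 1 degree of freedom.

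With no ties, this result does not depend on when within the 3 months people return. It is fixed by the group sizes alone.

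**Simulation with relapse, no predictor effect.** Return times are exponential among the 90% who return. The rate solves 0.9 × (1 − exp(−13λ)) = 0.82, so λ = −ln(1 − 0.82/0.9)/13 ≈ 0.186 per week. Follow-up is 52 weeks. Relapsers are counted as not at work at the visit. There are 200 runs per cell. Percentage of runs with p < 0.05 at n = 150:

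| Assumed relapse | 6 weeks | 3 months | 6 months | 12 months |
|---|---|---|---|---|
| 0% | 100 | 100 | 100 | 100 |
| 10% | 100 | 100 | 100 | 100 |
| 30% | 100 | 100 | 99 | 99.5 |
| 50% | 100 | 100 | 92.5 | 94.5 |
| 70% | 100 | 93 | 63.5 | 58 |
| 90% | 93 | 38 | 19.5 | 20 |

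A second set of runs put the low end at 50% relapse at about 87%, so roughly 87 to 100% is the fair range for that row. At n = 300 every cell up to 50% relapse is 99.5 to 100%.

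**Control.** Grouping the same kind of cohort at random (n = 150, 1,000 runs) gave 6.1% rejection. The Monte Carlo standard error is √(0.05 × 0.95/1000) ≈ 0.7 points, so this is in line with the nominal 5%. The grouping rule produces the rejections.

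**Sensitivity.** The results with relapse depend on the assumed 10% never returning. With a smaller share, nearly everyone off work at 6 or 12 months is a relapser, and rejection at those visits falls well below the ranges above. With a larger share it rises.

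**The case against.** **Relapse breaks the guarantee.** A reader might infer that the test is always significant. The article does not support that. It allows people to resume and go off work again, and heavy relapse mixes the groups, as the last rows of the table show. Very small samples also fall short: at n = 20 without relapse, rejection was between 68% and 100% across visits. This objection stands against the word always. It does not rescue the test, which answers no study question even when it fails to reject.

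**The authors may have meant something else.** The bracket could be a misplaced gloss on the outcome, with profiles meaning predictor profiles. The curves could also concern time to relapse, since resumption is partly operationalized that way; comparing early with later resumers on relapse would not be the event tested against itself. Neither is what the sentence says. It names rates of work resumption as the quantity compared, and the bracket defines the profiles. If another meaning was intended, the sentence still needs correcting.

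**The full plan may deal with it.** The article is condensed, but this is not an omitted detail. A grouping rule is stated, and the stated rule is circular.

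**The primary hypothesis does not depend on it.** This stands in full. Fear, avoidance and their generalization are tested by logistic regressions at each visit and by a time-dependent Cox model. Neither uses this grouping, nor does the sample size, and no stated decision rule uses the log-rank p-value. It would be wrong to infer that the primary analysis as a whole is invalid on this ground.

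**Conclusion.** The comparison is wrong as written and should be fixed. The groups are defined by a post-baseline reading of the event being analysed, so they differ largely by construction and the p-value is uninformative about any predictor.

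That conclusion rests on the text alone: the bracketed definition, the definition of resumption and the sick-leave criterion. The size rests on assumptions: 82% back at 3 months, 10% never returning, exponential return times and independent relapse. Under these, 150 completers give 100% rejection without relapse, 99 to 100% at 30% relapse and roughly 87 to 100% at 50%, against a nominal 5%. Near-certain significance is therefore supported for no or moderate relapse under those inputs, but not as a universal statement. Because the damage is limited to one supplementary comparison, should-fix is the right grade.

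**What to change.** Replace the bracketed definition with groups formed from variables measured before follow-up starts and not derived from the outcome. Prespecified groups of the preoperative PHODA-SeV harmfulness rating, the PASS-20 avoidance subscale or the generalization score from the computer task would serve. Say that formal inference comes from the Cox model with these predictors kept continuous, and that the curves illustrate it.

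Curves by work status may still be shown, but only as description and without a log-rank test. The same limit applies to a tempting alternative, thirds of a risk score from a Cox model fitted to the same data. Those groups are again derived from the outcome: with 12 pure-noise predictors and n = 150, a log-rank test across such thirds rejected in about 86 to 87.5% of simulated cohorts.

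The cost is one sentence. The suggested variables are already collected before surgery, so no new data are needed and the sample size is untouched.

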### Secondary objectives

Multiple linear regressions will be carried out to examine the effect of (generalization of) fear of movement-related pain and avoidance behavior, expectancies towards recovery and work resumption, and ÖMPSQ score on pain severity, disability, and quality of life. Interaction effects, including the interaction between the predictors and time, will be explored. Following potential confounders will be included as covariates in each analysis: age, sex, work characteristics, duration of incapacity for work, surgery complications, and the potential influence of the COVID-19 pandemic.

